- The presence or absence of erythema in E4, E5, and E6 will be evaluated and compared with N. A photograph of the non-irradiated and irradiated area will be retained. If erythema is observed, the MED will be set and the UVC dose in step 2 will be determined as in Figure 8. After determination of the MED for all 20 cases, Step 2 will be performed.

7) Determination of the irradiation dose in step 2

- Based on the lowest MED in all subjects, the irradiation dose in step 2 will be determined as in Figure 8.

| The lowest MED in all subjects | Irradiation dose in step 2 |
| --- | --- |
| No MED (No erythema with 500 mJ/cm^2^) | 500 mJ/cm^2^ |
| 500 mJ/cm^2^ | 400 mJ/cm^2^ |
| 400 mJ/cm^2^ | 300 mJ/cm^2^ |
| 300 mJ/cm^2^ | 200 mJ/cm^2^ |
| 200 mJ/cm^2^ | 100 mJ/cm^2^ |
| 100 mJ/cm^2^ | 50 mJ/cm^2^ |
| 50 mJ/cm^2^ | Discontinuation without step 2 |

Figure 8. MED in Step 1 and irradiation doses in Step 2

＜Step 2＞

8) UV irradiation

- Specify the irradiation range (40 x 40 mm) at three locations (S5, S30, B) on the back of the subject and irradiate with 222 nm UVC using the irradiation dose determined in 7. (Figure 9)
- Swab the surface of N0 with a swab (Elmex, Pro-media st-25) and submit it for culture testing.

40 mm

40 mm

NB

S5

S30

B

10 mm diameter

N5

N30

40 mm

40 mm

|  | UVC (+) | UVC (-) |
| --- | --- | --- |
| Swab：Pre-irradiation |  | **N0** |
| Swab：5 minutes after irradiation | **S5** | **N5** |
| Swab：30 minutes after irradiation | **S30** | **N30** |
| Biopsy：1 hour after irradiation | **B** | **NB** |

Figure 9．Irradiated area and irradiation doses➂

9) 5 minutes after irradiation

- Swab the surface of S5 and N5 with a swab and submit it for culture testing.

10) 30 minutes after irradiation

- Swab the surface of S30 and N30 with a swab and submit it for culture testing.

11) 1 hour after irradiation

- B and NB are locally anesthetized, skin tissue will be collected using a 3 mm diameter biopsy trepan (KAI Medical Co., Ltd., BP-30F) and immediately frozen and stored. Procced to step 12.

12) By seven days after biopsy

- Collect genomic DNA from biopsy tissue with QIAamp Blood Kit (QIAGEN, Cat. No. 51104 or 51106). The concentration of genomic DNA will be measured.

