# **13. Subject analysis (sub-group for effectiveness evaluation) and method of statistical analysis (primary/secondary analysis)**

A summary of the planned statistical analysis of this study is provided below. Details of the planned statistical analysis will be described in the statistical analysis plan. The summary of the planned statistical analysis described in this protocol may be changed in the statistical analysis plan. If the definition or analysis method for the primary endpoint is changed, the protocol will be amended.

1. Analysis populations

（1） Full analysis set (FAS)

The full analysis set (FAS) will consist of all subjects enrolled in the study, who have efficacy data available, excluding those without baseline data or significant protocol violations (e.g., absence of informed consent, enrollment outside the contract period).

（2）Per protocol set (PPS)

The per protocol set (PPS) will consist of the subjects in the FAS excluding those with any of the following significant protocol violations involving the study method, concomitant therapy, etc.:

- violation of the inclusion criteria
- violation of the exclusion criteria
- violation of prohibited concomitant medications
- violation of prohibited concomitant therapies

（3）Safety analysis set

The safety analysis set will consist of the subjects enrolled in this study who received any UV irradiation.

2．Target sample size and rationale

Target sample size: 20

This exploratory study will be conducted to gather information to properly design new clinical trials with patients. For this reason, the target number of cases was set in order to collect a wide range of efficacy and safety indicators. Theoretically, it is assumed that the possibility that 222 nm UVC will not cause erythema in the irradiated area is almost 100%. It is thought that this irradiation method will be judged to be appropriately safe when the one-sided 95% confidence interval lower limit is higher than 75%. In this study, the number of enrollment subjects will be gradually increased from 2 subjects to 20 subjects in total. If erythema does not appear in all 20 participants, the one-sided 95% confidence interval lower limit will be 83.9%. Since this test will be conducted as an exploratory one, when considering the implementation of the next phase of the test, the primary and secondary evaluation items will be comprehensively judged.

3．Items and plan of the statistical analysis

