The analysis will be performed after the completion of UV irradiation and sampling in all subjects. For all efficacy endpoints, the FAS will be used in the primary analysis, while the PPS will be used in a reference analysis. Safety will be analyzed using the safety analysis set.

(1) Safety analysis

1) Presence or absence of erythema

The erythema non-occurrence rate and its 95% confidence interval for each dose will be calculated.

2) Examination of DNA damage

The amount of CPD produced in the UV irradiation group and non-irradiation group will be compared using a paired *t*-test. If the amount of CPD produced is significantly higher in the irradiated group than in the non-irradiated group, it will be determined that there is DNA damage due to UV irradiation. The hypothesis testing will use a significance level of two-sided 5%, with the calculation of the two-sided 95% confidence interval.

3) Frequency of adverse events

A summary table will be prepared for the endpoint. For estimation of the proportion, the exact two-sided 95% confidence interval for a binomial distribution will be calculated per group. As necessary, Fisher’s exact test will be used for inter-group comparison.

(2) Efficacy analysis

1) Primary analysis

Bacterial detection frequency from skin swabs will be compared using the Χ^2^ test. The hypothesis testing will use a significance level of two-sided 5%, with the calculation of the two-sided 95% confidence interval.

2) Secondary analysis

The secondary efficacy endpoints will be analyzed for discussion to supplement the primary analysis results. No multiplicity adjustment will be performed in the analysis of secondary efficacy endpoints. The hypothesis testing will use a significance level of two-sided 5%, with the calculation of the two-sided 95% confidence interval.

(3) Interim analysis

No interim analysis is planned in this study.

(4) Independent data monitoring committee (IDMC)

An IDMC will not be established in this study.

(5) Final analysis

The final analysis will be performed after data from the subjects have been obtained and locked after the end of the follow-up period. The responsible biostatistician will prepare the “statistical analysis report” and submit it to the principal investigator.

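### Primary efficacy analysis: matched swabs from the same subjects are assigned an ordinary chi-squared test, which ignores the pairing and is usually conservative

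*Protocol*

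**What the plan says.** Under efficacy analysis, primary analysis, protocol section 13 says: "Bacterial detection frequency from skin swabs will be compared using the" chi-squared test. It adds: "The hypothesis testing will use a significance level of two-sided 5%, with the calculation of the two-sided 95% confidence interval". It does not mention pairing, McNemar's test or the two swab times.

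Section 8, Step 2, fixes where the swabs come from. The irradiated areas lie on each subject's own back: "Specify the irradiation range (40 x 40 mm) at three locations (S5, S30, B) on the back of the subject". At 5 minutes the instruction is "Swab the surface of S5 and N5 with a swab and submit it for culture testing", and S30 and N30 are swabbed in the same way at 30 minutes. One further swab, N0, is taken from a non-irradiated area before irradiation. Each subject thus gives five swabs, four of which form two irradiated/control pairs.

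The subjects are those of Step 1: "After determination of the MED for all 20 cases, Step 2 will be performed". The number is given as "Target sample size: 20".

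For CPD, measured on biopsies B and NB from the same back, section 13 says that the "UV irradiation group and non-irradiation group will be compared using a paired" t-test.

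Section 7 lists the bactericidal effect as a secondary endpoint. The primary endpoint is erythema at 24 hours.

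**The concern.** A chi-squared test on a two-by-two table assumes that the two rows are independent samples. Here each row holds the same 20 people. A subject with a dense skin flora is likely to be positive at both sites, and one with a sparse flora negative at both. The information on the irradiation effect lies in the subjects whose two sites disagree, and the chi-squared test never looks at them.

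This is the only test that the protocol names for bactericidal effect, and section 13 says that primary and secondary items will be weighed together when the next phase is considered. If the test is run as written, the p-value and interval will not describe the data collected. The most likely consequence is that a real effect is missed or reported with too much uncertainty. The within-subject design, which is what makes 20 subjects informative, would be wasted.

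**Working it through.** **Inputs.** From the protocol: 20 subjects, one irradiated and one control swab per subject at 5 and at 30 minutes, chi-squared test, two-sided 5%, 95% interval. The protocol gives no detection rate, within-subject correlation or power for this test, so there is no planned figure to reproduce. Its one computed design figure, 83.9%, concerns erythema. The rates and correlations below are assumptions, shown over a range.

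**1. One table, three pairings.** Assume control 16/20 positive and irradiated 10/20 positive.

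Pearson chi-squared = 40 × (16×10 − 10×4)² / (20×20×26×14) = 576,000/145,600 = 3.956, p = 0.047. Independent-samples interval: variance (0.8×0.2 + 0.5×0.5)/20 = 0.0205, so 0.30 ± 1.96×0.143 = 1.9% to 58.1%. Neither result changes with the pairing.

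Let b be the subjects positive at the control site only and c those positive at the irradiated site only. Then:
- McNemar asymptotic: (b − c)²/(b + c) on 1 df.
- Mid-P: 2·P(X ≤ c) − P(X = c), with X ~ Bin(b + c, ½).
- Paired Wald variance: [(b + c) − (b − c)²/20]/400.

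| b/c | Both positive | Pearson p | McNemar asymptotic p | Mid-P | Exact p | Paired 95% interval |
|---|---|---|---|---|---|---|
| 6/0 | 10 | 0.047 | 0.014 (36/6 = 6.0) | 1/64 = 0.016 | 0.031 | 9.9% to 50.1% |
| 8/2 | 8 | 0.047 | 0.058 (36/10 = 3.6) | 67/1024 = 0.065 | 0.109 | 1.9% to 58.1% |
| 10/4 | 6 | 0.047 | 0.109 (36/14 = 2.57) | 1941/16384 = 0.118 | 0.180 | −4.2% to 64.2% |

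Within-pair covariance is (both positive)/20 − 0.8×0.5. This is +0.10, 0 and −0.10 down the table. The first row is the expected pattern: the interval is narrower once pairing is used. In the second row pairing carries no information, so the two intervals coincide and the p-values differ only through the form of the test. The third row needs negative correlation.

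A case where the planned test misses: 15/20 v 9/20 with discordant pairs 6/0 gives Pearson p = 0.053, against 0.014 asymptotic and 0.016 mid-P.

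**2. Long-run behaviour at one time point.** Simulation of 20 pairs with a normal subject effect on the logit scale. Type I error is at 50% detection in both conditions, power at 59% v 25%, nominal 5%.

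| Subject logit SD | Chi-squared type I error | Power: chi-squared | Power: exact McNemar | Power: mid-P McNemar |
|---|---|---|---|---|
| 0 | 4.4% | 59% | 45% | 55% |
| 2 | 1.0% | 60% | 60% | 72% |
| 4 | 0.2% | 60% | 69% | 83% |

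At SD 1 the chi-squared type I error is 2.7%.

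**3. A second correlation model.** Normal latent variable, 60% detection in both conditions. At latent correlation 0, 0.3, 0.5, 0.7 and 0.9, chi-squared type I error is 4.9%, 2.9%, 1.6%, 0.6% and 0.1%. Asymptotic McNemar stays at 4.3% to 4.9% up to 0.7 and is 2.8% at 0.9. Exact McNemar is 2.2% at correlation 0 and 0.2% at 0.9.

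Both models agree: with positive correlation the planned test runs well below its nominal level, and it gains almost no power as the correlation rises.

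**The case against.** **The trial is exploratory and the endpoint secondary; the SAP may change the summary.** This stands as a limit on the consequences. The sample size does not rest on the swab test, and neither does any dose or safety rule. But the protocol names the test, the level and the interval, and it requires a protocol amendment only for changes to the primary endpoint, so nothing in it forces a correction here.

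**The wording could be read to include McNemar's test, itself a chi-squared test.** That is possible but not the natural reading, since the same section says paired where it means paired.

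**The paired test is not always better.** This stands. With no within-subject correlation, mid-P McNemar has about 55% power against 59% for chi-squared. Exact McNemar is itself conservative with 20 pairs: its type I error is about 1.3% at SD 2 and 0.35% at SD 4, and it only matches chi-squared on power at SD 2. It is not the natural replacement.

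**A reader might infer that the planned test also produces false positives.** The documents do not support that as a general statement. Tables such as 5/20 v 0/20 (chi-squared 0.017, exact McNemar 0.063) or 20/20 v 16/20 (0.035, 0.125) look like evidence. In each, however, one condition is constant, so pairing carries no information and the gap comes from the conservatism of the exact test. Asymptotic McNemar gives 0.025 and 0.046. Inflation would need negative correlation, or pooling of the two times with correlation concentrated within a condition. In a pooled 40 v 40 simulation, type I error was 1.9% with a shared subject effect only (0.5), 8.8% with 0.1 subject and 0.5 subject-by-condition correlation, and 12.5% with 0 and 0.8. The protocol does not say that the times are pooled.

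**A reader might extend the point to adverse events, where "exact test will be used for inter-group comparison".** That test is to be used only as necessary. No adverse-event groups are defined, and irradiated and control sites are not matched one to one (six to one in Step 1, three to four in Step 2). The text is too thin to call it the same error.

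**Conclusion.** The point holds. The chi-squared test is wrong as written for swabs matched within the same 20 subjects, and it is inconsistent with the paired test for CPD in the same section.

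For a contrast at one time, the expected error is conservative: true type I error of about 1% or less at nominal 5% once the subject logit SD is 2 or more, an interval that is too wide, and at 59% v 25% detection a loss of about 12 points of power at SD 2 (72 − 60) and 23 at SD 4 (83 − 60). In any single data set the p-value may lie on either side of the paired one, because it does not depend on the discordant pairs. That is not a systematic risk of false claims.

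The sizes rest on assumed detection rates and positive within-subject correlation, neither of which the protocol gives. That the test does not fit the design rests on no assumption beyond reading the named test in its ordinary sense. The primary endpoint and the erythema conclusion are not affected.

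**What to change.** In section 13, primary efficacy analysis, replace the chi-squared test with McNemar's test for S5 v N5 and for S30 v N30 separately, and report the paired difference in detection with a 95% interval suited to small samples, such as the Tango score interval. Name one form in advance, mid-P or asymptotic. If the two times are to be combined, use a method that accounts for subject and say so; do not treat the swabs as independent. Because separate times make two tests explicit, state whether both are reported unadjusted.

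The cost is analysis wording in the protocol, carried into the SAP. No extra subjects, swabs or procedures are needed. The one statistical price is a few points of power (about 55% v 59% in the case shown) if the two sites on one back prove to be uncorrelated.

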# **14．Quality assurance of the trial**

1. Quality control

Monitoring of the study will be performed to periodically check whether this study is conducted safely in accordance with the protocol and whether the data are properly collected.

(1) Appointment of the responsible monitor and other monitors

The principal investigator will appoint the responsible monitor and other monitors for this study.

(2) Implementation of study monitoring

1) Monitoring on subject data

The monitor will check the CRFs (accumulated database) submitted to the data center throughout the study period. As necessary, direct reviews of source documents (e.g., informed consent forms, medical charts, CRFs) and off-site monitoring will be performed at Kobe University Hospital. The items to be checked at monitoring are specified in the “Written procedure for implementation of study monitoring”.

2) Monitoring on non-subject data

The monitor will perform study monitoring before, during, and after the end (discontinuation or suspension) of the study. The items to be checked at monitoring are specified in the “Written procedure for implementation of study monitoring”.

2．Quality assurance

In this exploratory study, performed in a small number of patients, no auditing is planned.

# **15．Consideration of human rights and safety/disadvantages to the subjects**

1) Consideration of human rights (privacy protection)

The protection of the subject's privacy should be considered when preparing the CRF and handling the subject's data. That is, the name and initials of the subject are not to be used but are specified by the subject identification code. The principal investigator creates a correspondence table (subject identification code table) of the medical record number, patient name, date of birth, and patient identification code set in the facility. The subject identification code table is kept by the principal investigator.

2) Consideration of safety and disadvantages

If a subject suffers health injury related to the study, the sub-investigator will perform appropriate action and treatment. It should be described that information necessary for conducting clinical research safely is collected and reviewed, and the research protocol could be changed as necessary.

# **16．Expenses for the subjects**

1) Compensation for health injury

If a subject suffers health injury related to this study, the sub-investigator will perform appropriate action and treatment. For compensation of health injury, the “Ethical Guidelines for Medical and Health Research involving Human Subjects” will be followed. Thus, a clinical study liability insurance policy will be taken out to be able to compensate for death or permanent disability (grade 1 to 14 permanent disability) resulting from this study. For other health injury, the tests, treatments, and other necessary procedures will be performed within the range of medical services covered by the subject’s health insurance.

2) Participation in liability insurance

In preparation for liability, the principal investigator or sub-investigators will participate in liability insurance.

# **17．Compliance with ethical guidelines including the Declaration of Helsinki**

This study will be conducted in compliance with the Ethical Guidelines for Medical and Health Research involving Human Subjects (Notice of Ministry of Health, Labour and Welfare. December 22, 2014), the Declaration of Helsinki, and Kobe University Conflicts of Interest Management Guideline.

# **18．Retention of recorded documents**

In accordance with the “Guideline on the study data storage period at Kobe University Graduate School of Medicine etc.”, the study representative will retain the study-related important documents (e.g., copies of the application forms submitted to the ethics review committee, notification documents from the head of the research institution, copies of various application forms and reports, documents for data disclosure, and other documents or records supporting the information used in the study including the data correction log and description in notebooks) in a lockable place, either until 10 years after study discontinuation/completion or 10 years after the date of publication of the study results in the literature etc., whichever is later. Thereafter, the documents will be destroyed after subject individuals are made non-identifiable.

At each collaborative research implementing entity, the study data etc. will be appropriately retained for the duration required by the rules of the collaborative research implementing entity.

# **19．Registration of research program**

Based on counsel by the International Committee of Medical Journal Editors (ICMJE), this research program was registered to University Hospital Medical Information Network-Clinical Trial Registry (UMIN-CTR) at the start of this research (UMIN ID: 000027449).

# **21．Disclosure of research funding sources and COI status of researchers**

Although there are companies that are related to a COI regarding the planning, implementation, and publication of this study, they are managed so as not to unduly affect the study results. This study is an independent clinical study and is funded by the research expenses of the department to which the principal investigator belongs, and is partly implemented with provision of UV irradiation equipment and partial funding from Ushio Inc., based on a contract between Ushio Inc. and Kobe University.

# **22．Change of study protocol**

Changes (revisions) of the study protocol, informed consent form will be made after obtaining approval from the ethics committee of the medical institution in advance.

# **23．Publication of research results**

The contents of this research will be presented at the appropriate international and domestic conference and be published in a peer reviewed journal after the study completion.

